						**Age (2 levels)**		
**All (community population)**					**N = 1280**	**N = 640**	**N = 4074**	**N = 2037**
	Access to tobacco: If try buy, likely to be successful^1^	32%-25%	680	999	>0.80	0.80	>0.99	>0.99
	Access to tobacco: If try buy, likely to be successful^2^	32%-22%	328	479	>0.99	>0.80	>0.99	>0.99
	Awareness tobacco marketing in shops^1^	81%-22%	14	19	>0.99	>0.99	>0.99	>0.99
	Awareness tobacco marketing in shops^2^	81%-71%	305	445	>0.99	>0.99	>0.99	>0.99
	Perceived prevalence regular smoking^1^	62%-46%	164	238	>0.99	>0.99	>0.99	> 0.99
	Perceived prevalence regular smoking^2^	62%-52%	404	591	>0.99	>0.80	>0.99	>0.99
	Incidence regular smoking^3^	4%-2%	1239	1797	>0.80		>0.99	>0.80
	Incidence any smoking^3^	9%-7%	2987	4396			>0.80*	
	Prevalence regular smoking^3^	13%-10%	1841	2707			>0.99	>0.80
	Prevalence regular smoking^3^	13%-9%	1009	1478	>0.80		>0.99	>0.80
**Current smokers**					**N = 136**	**N = 68**	**N = 482**	**N = 241**
	Purchase tobacco from shops^4^	55%-43%	412	603			>0.80	0.82*
	Purchase from Supermarkets^4^	12%-5%	389	563			>0.80	0.85*
	Purchase from Small Shops^4^ (increase after POS Supermarkets	44%-56%	411	603			>0.80	0.82*
	Purchase from Small Shops^4^	44%-32%	393	575			>0.80	0.84*
	Access to tobacco: If try buy, likely to be successful	32%-20%	408	596			>0.80	0.83
	Awareness tobacco marketing in shops^1^	81%-22%	14	19	>0.99	>0.99	>0.99	0.99
	Awareness tobacco marketing in shops^2^	81%-71%	305	445			>0.80	0.80*
	Perceived prevalence regular smoking^2^	62%-50%	404	591			0	0.83*
**Ever smokers**					**N = 422**	**N = 212**	**N = 1287**	**N = 644**
	Purchase tobacco from shops^4^	23%-16%	530	776	>0.80*		>0.99	0.87
	Purchase from Supermarkets^4^	4%-1%	489	697	>0.80*		>0.99	0.85*
	Purchase from Small Shops^4^ (increase after POS Supermarkets )	18%-25%	568	832	>0.80*		>0.99	0.85
	Purchase from Small Shops^4^	18%-12%	588	859	>0.80*		>0.80	>0.80*
	Access to tobacco: If try buy, likely to be successful^2^	32%-22%	408	596	>0.80		>0.99	>0.80
	Awareness tobacco marketing in shops^1^	81%-22%	14	19	>0.99	>0.99	>0.99	>0.99
	Awareness tobacco marketing in shops^2^	81%-71%	305	445	>0.80		>0.99	>0.99
	Perceived prevalence regular smoking^2^	62%-52%	404	591	>0.80		>0.99	>0.80

1 Change based on findings McNeil et al. [14] paper on the removal of Point of Sale tobacco displays in Ireland.

2 Starting percentage based on findings McNeil et al. [14] paper on the removal of Point of Sale tobacco displays in Ireland.

3 Starting percentages based on findings latest published results from HBSC [19] and SALSUS [18] studies.

4 Starting percentages based on findings latest published results from SALSUS [18].

* Denotes power calculation for a one-tailed test. Blank cells are underpowered to detect a significant change.

The estimated baselines and changes in access to tobacco; awareness of tobacco marketing; perceived prevalence of youth smoking; and ease of access to tobacco are based on the evaluation of POS ban in Ireland. [14] The baseline percentages for other intermediate outcomes outlined in below are derived from data from the 2008 Scottish Schools Adolescent Lifestyle and Substance Use Survey (SALSUS) National Report [18] and the Health Behaviours of School Children (HBSC) 2010 Scotland National Report [19]. Power calculations are given for all pupils (community populations), current smokers and ever smokers. An asterisk denotes power calculation for a one-tailed test. Blank cells are underpowered to detect a significant change.

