## Background

Tobacco advertising and marketing activity have been shown to have a direct impact on adolescent smoking intentions, perceived smoking prevalence and youth smoking prevalence [1,2]. In addition, a dose–response relationship has been demonstrated between adolescent tobacco marketing awareness and smoking uptake [3]. Following an EU directive [4], the Tobacco Advertising and Promotion Act (TAPA) was implemented in the UK between 2003 and 2005 [5]. The legislation bans advertising on billboards, in cinemas and print media, by direct mail, on-pack promotions, and through brand sharing and international tobacco sponsorship. On 29^th^ April 2013, point of sale (POS) tobacco advertising was banned in large retailers in Scotland [6]. POS advertising in smaller retail outlets is now one of the few ways in which the tobacco industry can legitimately promote their products in Scotland. The ban will be extended to include these retail outlets in April 2015 [6]. The gantries currently used to display tobacco products are usually supplied by the tobacco industry and sited in prominent in-store positions, most often at checkouts, with products arranged attractively and sometimes positioned in such a way as to obscure health warnings [7]. Recent UK research [8,9] and a systematic review [10] have found that, in children, POS displays increase susceptibility to smoking, experimentation and initiation into smoking. These displays may also influence perceived prevalence of smoking and the perception that tobacco products are easily obtained and are a ‘normal’ product. Studies of adults suggest that POS advertising increases impulse cigarette purchases [11]. Positioning of POS displays may also be important in that cigarette retailers located in communities with a high proportion of children have been shown to be more likely to display cigarettes near children’s products [12]. A multi-centre Canadian study also found that stores near schools with high smoking prevalence had significantly lower mean price per cigarette, more in-store promotions (price, gift or bonus promotions) and fewer government-sponsored health warnings [13].

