### Research questions

Our specific research questions are:

1. Does implementation of POS regulations in the TPMS Act in i) supermarkets alone (partial ban); and ii) all tobacco retailers (complete ban) result in changes in exposure to tobacco advertising in young people aged 12 to 17 years?

2. Is a reduction in exposure to POS advertising associated with: changes in brand awareness; perceived accessibility of tobacco; perceived prevalence of youth smoking; susceptibility to smoking; and the incidence and prevalence of smoking in young people aged 12 to 17 years?

3. Is there any evidence of socio-economic patterning in any of the attitudinal or behavioural outcomes in young people?

4. What is the association between area-level deprivation and i) levels of POS tobacco advertising and availability of cigarettes pre-and post-legislation; or ii) enforcement of the legislation when implemented?

5. Is there any evidence of a dose-response relationship between changes in exposure to POS advertising and interim and longer-term outcome measures in young people?

6. Are there any unintended adverse consequences associated with the legislation, for example, an increase in cigarette purchases from black-market sources?

7. Is there any evidence of changes in POS advertising and marketing strategies in the lead up to implementation of measures in the TPMS Act in either supermarkets or small retailers?

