Data governance requires that the identity of all retail sites audited and all panel participants approached to take part in an interview remain confidential. In line with these requirements all sites and participants have been assigned non-identifiable codes to retain anonymity. Identifiable data (e.g. participants, premise names and address details) are held on a separate database and will be linked to electronic data files using these non-identifiable codes. Technical reports, presentations and publications will ensure that no participants or retail premises can be identified.

3. Annual school surveys of secondary school pupils

The school survey has a repeat cross-sectional design with embedded cohorts (Additional file 1: Table S1). We hypothesise that implementation of a partial ban on POS adverting (larger retailers only) will have only a small impact on awareness and attitudes. In order to assess this assertion, baseline surveys of S2 (age 13) and S4 (age 15) pupils were conducted in each of the four study schools between February and March 2013. This survey will be repeated one year later. The impact of the Scottish partial POS ban on 13-and 15-year-olds will then be compared with the impact on a similar age group of the comprehensive POS ban in Ireland, where legislation was implemented simultaneously in both large and smaller retailers in 2011 [14].

To assess the impact on the implementation of POS legislation in smaller retailers in 2015, a second baseline survey will be conducted with all pupils (S1-6) from our study schools in February to March 2015, with repeat surveys conducted annually for two years post-implementation. This survey series will allow us to measure the impact of a comprehensive ban (supermarkets and smaller retailers) on POS advertising on behavioural outcomes including smoking incidence and prevalence, as well as on brand awareness and other attitudinal outcomes.

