**Table 3 T3:** Power calculations for intermediate and long-term outcomes

			**Sample size required at 0.80 power with two-tailed test**		**Sample before and 1 year after POS Supermarket (4 S2 & 4 S4 from 4 schools 24 pupils each class 85% response rate)**		**Sample before Small Shops POS and 2 years after (all pupils attending schools, 4 schools, school size 1200 pupils, response rate 85%)**	
	**Outcome**	**Change**	**p < .05**	**p < .01**	**4 schools combined**	**Urbanisation (2 levels)**	**4 schools combined**	**Urbanisation (2 levels)**
						**Deprivation (2 levels)**		**Deprivation (2 levels)**

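### Table 3 states power for a rise in small-shop purchases after the supermarket ban in the 2015-17 sample, which has no wave before that ban

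*Protocol article*

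**What the plan says.** The Background dates the first stage of the ban to 29 April 2013, when "point of sale (POS) tobacco advertising was banned in large retailers in Scotland". Under the annual school surveys in Methods/design, "baseline surveys of S2 (age 13) and S4 (age 15) pupils were conducted in each of the four study schools between February and March 2013", and "This survey will be repeated one year later". For the smaller retailers, "a second baseline survey will be conducted with all pupils (S1-6) from our study schools in February to March 2015", followed by two annual repeats.

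The column headings of Table 3 follow the same division. One pair is headed "Sample before and 1 year after POS Supermarket". The other is headed "Sample before Small Shops POS and 2 years after (all pupils attending schools, 4 schools, school size 1200 pupils, response rate 85" (per cent).

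The row "Purchase from Small Shops^4^ (increase after POS Supermarkets" appears twice, and its cells read:

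| Group | Change | 2013-14, all / subgroup | 2015-17, all / subgroup |
|---|---|---|---|
| Current smokers | 44%-56% | blank / blank | >0.80 / 0.82* |
| Ever smokers | 18%-25% | >0.80* / blank | >0.99 / 0.85 |

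The table notes explain that an asterisk marks a one-tailed calculation and that a blank cell is underpowered.

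**The concern.** A change after the supermarket ban has to be measured against data from before April 2013. The 2015-17 sample has none: its own baseline already lies under the partial ban. Because blank means underpowered, a filled cell tells the reader that the comparison is adequately powered. The four filled 2015-17 cells therefore credit the study with power for a contrast that this sample cannot estimate.

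The same row in the 2013-14 columns, where the contrast can be estimated, is either blank or claimed only one-tailed. A reader who takes >0.80 or >0.99 from the row could treat a null result as evidence that purchases did not move to small shops, when the usable comparison had limited power to show such a move.

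**Working it through.** **Inputs (Table 3).** Rates 44% to 56% (current smokers) and 18% to 25% (ever smokers). Sizes per wave in 2013-14: 136 current (68 per subgroup) and 422 ever smokers. Sizes per wave in 2015-17: 482 (241 per subgroup) and 1287 (644 per subgroup). Alpha is 0.05. Clustering within schools is not allowed for; the table's figures reproduce without it.

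**Formula.** For two independent proportions with n per wave, d = |p1 − p2| and p̄ = (p1 + p2)/2,

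power = Φ{ [d − c − z·√(2p̄(1−p̄)/n)] / √[(p1(1−p1) + p2(1−p2))/n] },

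with z = 1.960 two-sided or 1.645 one-sided, and c = 0 without or 1/n with continuity correction.

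**Step 1: reproduce the 2015-17 cells, using the 2015-17 size in both periods.**

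| Group, n per wave | Test | Without / with correction | Stated |
|---|---|---|---|
| Current, 482 | two-sided | 0.962 / 0.957 | >0.80 |
| Current, 241 | one-sided | 0.841 / 0.817 | 0.82* |
| Ever, 1287 | two-sided | 0.991 / 0.990 | >0.99 |
| Ever, 644 | two-sided | 0.865 / 0.849 | 0.85 |

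The arithmetic is sound, and the two exact entries match with the continuity correction. They do so only if a wave of 482 or 1287 smokers stands on both sides of the comparison. No wave of that size precedes April 2013.

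The required sizes for ever smokers (568 at p < .05, 832 at p < .01) also reproduce exactly with the correction. Those for current smokers (411/603) do not fit 44%-56%, which needs 288/421; they fit 44%-54%. That is a separate slip.

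**Step 2: compute power where the contrast exists, 2013 v 2014.**

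- Current smokers, n = 136, d = 0.12, p̄ = 0.50. The null standard error is √(2 × 0.25/136) = 0.0606 and the alternative is √(0.4928/136) = 0.0602. Two-sided, uncorrected: (0.12 − 1.960 × 0.0606)/0.0602 = 0.02, power 0.508. With correction (1/136 = 0.0074): −0.10, power 0.459. One-sided: 0.632 / 0.585.
- Ever smokers, n = 422, d = 0.07, p̄ = 0.215. The null standard error is √(2 × 0.215 × 0.785/422) = 0.0283 and the alternative is √(0.3351/422) = 0.0282. Two-sided, uncorrected: (0.07 − 1.960 × 0.0283)/0.0282 = 0.52, power 0.697; with correction 0.667. One-sided, uncorrected: (0.07 − 1.645 × 0.0283)/0.0282 = 0.83, power 0.798; with correction 0.773.

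The current-smoker blank is right. The ever-smoker >0.80* falls short by 0.002 without correction and by about 0.03 with the correction that the table uses elsewhere.

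**Step 3: can 2015 data restore the power?** Add S2/S4 in 2015 to 2014. Table 2 gives 168 + 333 = 501 ever smokers, so 422 v 923, and 35 + 126 = 161 current smokers, so 136 v 297. With the unequal-n form of the formula, two-sided power is 0.80-0.82 (ever) and 0.60-0.64 (current), but only if the samples are independent. The S2 year group of 2013 is the S4 year group of 2015 in the same four schools. Leaving out the 2015 S4 pupils gives 422 + 168 = 590 and 136 + 35 = 171 after the ban, with power 0.73-0.76 and 0.51-0.55.

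**The case against.** The strongest defence is that this is a labelling slip with little consequence. Four parts of it deserve weight.

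- **Status of the outcome.** A reader might infer that a shift to small shops is a named hypothesis or a listed unintended consequence. The article does not support that. Research question 6 asks "Are there any unintended adverse consequences associated with the legislation" but gives black-market purchases as its example. Outcome measures adds proxy purchases and new strategies to get round the rules. The hypothesis stated for the partial ban concerns awareness and attitudes. The shift to small shops appears only as a row in Table 3.
- **Use of the cells.** Data analysis brings in purchase of tobacco with implementation in smaller retailers, not with the supermarket phase. The four cells feed no primary analysis stated for the supermarket ban, so a misread null is a risk and not a certainty.
- **Disclosure.** The blank 2013-14 cells already admit low power for current smokers and for the ever-smoker subgroups, and the asterisk declares the one-tailed test. It would be wrong to say that the table hides this.
- **Size of the miss.** Uncorrected, 0.798 against >0.80 is a rounding-level shortfall. The larger gap is between the one-tailed figure and 0.67-0.70 two-sided.

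None of this rescues the four 2015-17 cells. They cannot stand for the change from 2015 to 2017, which concerns the small-shop ban and has its own rows in the opposite direction (44%-32%, 18%-12%). Nor can they stand for 2013 against 2015: the column heading says otherwise, the article describes no such comparison, and it would set S2/S4 against S1-S6. For current smokers (136 v 482) that comparison would reach only about 0.70 two-sided even without correction.

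**Conclusion.** The four 2015-17 entries are wrong as written. Their arithmetic is right for the sizes used, but the sample has no wave before the supermarket ban and cannot estimate the change that the row names. On 2013 against 2014, two-sided power is 0.46-0.51 for current smokers and 0.67-0.70 for ever smokers; the one-sided 0.77-0.80 for ever smokers just misses the stated >0.80*.

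These figures assume independent samples of the sizes in Table 3, the rates in the row, alpha 0.05 and no clustering; the ranges run from with to without continuity correction. A stricter alpha, which Data analysis foresees where possible, would lower them.

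The point is confined to this row. It does not show that the study fails a stated hypothesis or that a planned primary analysis is underpowered.

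**What to change.** 1. In Table 3, blank the four 2015-17 cells in the two rows on increased small-shop purchases after the supermarket ban.
2. Restate the ever-smoker 2013-14 combined cell as about 0.67-0.70 two-sided (0.77-0.80 one-sided).
3. Add one sentence: any shift of purchases to small shops after the supermarket ban is assessed on S2/S4 in 2013 against 2014 as an underpowered, exploratory comparison, and a null result is not evidence of no shift.

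This costs a table correction and a sentence, with no new data. Adding the 2015 S2/S4 wave is optional. It should not be credited with 0.80-0.82, because one year group recurs, and because the article itself expects more industry activity in the run-up to the 2015 ban, which could affect that wave.

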### Data analysis

An advantage of adopting a spatial approach to data collection is that the various quantitative datasets can be readily integrated into a GIS. By collecting postcodes, the retail outlets, audits (retailer panel and discreet) and the school survey information will each be geographically referenced. This will enable us to integrate the data into a single database for further quantitative analysis.

The primary analyses around implementation in large retailers will focus on estimating the reduction in POS advertising between February and April 2013 (baseline) and February-to April 2014 and the relationship between POS exposure and awareness of POS advertising and changes in perceived access to tobacco and perceived youth smoking prevalence. In addition to the above, the primary analyses around implementation in smaller retailers will also examine the impact of full implementation on behavioural outcomes including purchase of tobacco products and smoking incidence and smoking prevalence. Specifically, we will:

•Examine changes in exposure to tobacco advertising, access to tobacco products and attitudes towards smoking between baseline (February to April 2015) and the same months in 2016 and 2017 for the total sample, with sub-group analyses by community deprivation, urbanisation and baseline availability of cigarettes.

•Examine changes in incidence of regular smoking and smoking prevalence between baseline (February to April 2015) and the same months in 2016 and 2017, with sub-group analyses by community deprivation, urbanisation and baseline availability of cigarettes.

•Assess if there is a of a dose-response relationship between changes in POS advertising or changes in availability of cigarettes and other study outcomes. To do this, we will create continuous dummy variables for various measures of advertising exposure which can be used in the analyses.

Given the number of outcomes we wish to examine, in the analyses we will set a higher statistical significance threshold (type I or α error) where possible.

Focus group interviews will be fully transcribed and the data entered into the qualitative computer package NVivo, version 10. The data will be coded and will undergo inductive thematic analysis employing constant comparison to identify key themes, focussing on uncovering the social worlds of the participants, and examples of differing views and experiences. The findings will be used to interpret findings from the quantitative components, in particular, any differences associated with community deprivation or baseline availability of cigarettes, or baseline availability of cigarettes through retail and/or black-market sources. Findings from the focus groups will be reviewed annually in order to identify emergent issues that should be explored further in the school survey.

After each wave of data collection, quantitative and qualitative data will be synthesised using a multi-level approach. First, quantitative data from the mapping, retailer audit and school surveys will be synthesised (Synthesis 1) followed by a synthesis of qualitative data from the focus groups and additional qualitative data from other study components (Synthesis 2). The products of syntheses 1 and 2 will then be combined using a series of mixed methods matrices, which allow the juxtaposition of findings from the different components of the study. We will then use these to generate a narrative synthesis (Synthesis 3). The focus in Synthesis 3 will be on consistencies and contrasts in the data which will form the basis for short interim reports. Once data collection is complete, the synthesis of data across all the study waves will follow a similar process but the focus of the analyses will change over time.

Findings from our study will be placed in a broader context through comparison with national level data. In particular, we will compare levels of compliance in tobacco retail outlets in our study communities with national data collected by Trading Standards Officers. Using data from the national register of tobacco outlets, we will also compare the density (and changes in density) of outlets in the four study communities to all other communities across the country. In addition, findings about changes in availability and sources of cigarettes for under-age smokers for our study populations will be compared with national data available from the Scottish Adolescent Lifestyle and Substance Use Survey (SALSUS) [18].

## Discussion

The POS legislation presents a unique opportunity to examine the impact of a public health policy and, as far as we are aware, this is the first study to robustly assess the impact of a partial and comprehensive ban of POS tobacco advertising on youth attitudes to smoking, perceived access to tobacco products and smoking prevalence. In addition, we will also monitor compliance with the legislation and changes in tobacco retailing and marketing activity, as well as any unintended consequences associated with the legislation, such as new tobacco industry tactics and black-market sales. We have developed a systematic and robust evaluation that overcomes many of the methodological problems inherent in a natural experiment. Through careful design of a multi-component study we will be able to assess differential impacts associated with the legislation by both community deprivation and individual measures of socio-economic status. We will also develop novel approaches, both to the measurement of exposure to point of sale tobacco advertising and depicting changes in spatial and temporal distribution of some of the potential determinants of health inequalities.

The major methodological challenge associated with evaluating the impact of the POS legislation is that it came into force simultaneously across all regions in Scotland. Therefore, neither randomisation nor the use of geographical controls is possible. Instead, we chose an uncontrolled before and after design as the only feasible design. This poses a threat to internal validity and the inference of causation, however, a number of measures to overcome this problem have been included in the design. We have included a set of outcomes on other health behaviours in the school survey, which are unrelated to the legislation and assess change over time in our community populations, thus providing an internal control. We will also assess whether there is a dose response relationship between our measures of tobacco marketing exposure and our short-, intermediate and long-term outcomes - a powerful indicator of cause and effect [21]. In our interpretation and synthesis of the data we will use triangulation, placing greatest weight on outcomes which are confirmed by multiple data sources [22]. Finally, we will collect information on changes in policy/practice and other confounding factors both locally and nationally that could influence the outcomes. This will allow us to eliminate alternative interpretations of the study findings before inferring causation.

Another large-scale evaluation of public policy, the evaluation of Scotland’s smoke-free legislation [23], had a significant impact on the implementation of smoke-free legislation in other jurisdictions. Should the evaluation find that POS legislation has an impact on brand awareness in young people, initiation into smoking and/or smoking prevalence, then this will encourage policy makers in other jurisdictions to develop and implement similar legislation.

